**6.2.4.3. Haematology and Clinical Chemistry**

Blood samples will be taken at each visit EXCEPT 4 and 6 (as indicated in Table 1) for routine haematology and clinical chemistry testing. All samples will be transferred to a central laboratory (Quest Diagnostics) for analyses. Sample handling and shipping instructions will be provided separately.

Parameters to be tested are listed below.

**Biochemistry**

|               |                 |            |                      |
|---------------|-----------------|------------|----------------------|
| Total Protein | LDH             | Uric Acid  | Potassium            |
| Albumin       | Total Bilirubin | Calcium    | Chloride             |
| ALT (SGPT)    | Urea Nitrogen   | Phosphorus | Bicarbonate          |
| AST (SGOT)    | Creatinine      | Sodium     | Alkaline Phosphatase |
| GGT           |                 |            |                      |

**Haematology**

|                |                     |                                    |
|----------------|---------------------|------------------------------------|
| Platelet Count | RBC Indices: | WBC Count                          |
| RBC Count      | MCV                 | Automated WBC Differential: |
| Haemoglobin    | MCH                 | Neutrophils                        |
| Haematocrit    | MCHC                | Lymphocytes                        |
|                |                     | Monocytes                          |
|                |                     | Eosinophils                        |
|                |                     | Basophils                          |

**6.2.5. Pregnancy**

Women of child-bearing potential should be taking adequate contraceptive measures (Section 5.2.1). However, in the unlikely event of pregnancy occurring during dosing with study medication or the follow-up period, details must be documented and reported to GSK. In addition any pregnancies brought to the attention of the investigator after this

period, and where it is known that study medication was taken at the time of conception, must also be reported.

Any pregnancies identified during the screening phase/prior to study medication administration do not need to be collected.

#### **6.2.5.1. Pregnancy Testing**

A urinary  $\beta$ -HCG pregnancy test will be performed for females of child-bearing potential at each visit during the study. If positive, a blood sample will be collected and sent to Quest Diagnostics who will perform a serum  $\beta$ -HCG test as confirmation.

#### **6.2.5.2. Time Period for Collecting Pregnancy Information**

The time period for collecting information on the occurrence of pregnancy will be identical to the time period for collecting AEs and SAEs as described in Section 10. However, pregnancies identified during the screening phase and prior to study medication administration do not need to be collected.

#### **6.2.5.3. Action to be Taken if Pregnancy Occurs**

Any female patient who becomes pregnant during the course of the study will be discontinued from study medication. The investigator, or his/her designee, will collect pregnancy information on the patient. The investigator, or his/her designee, will record pregnancy information on the appropriate form and submit it to GSK within 2 weeks of learning of a patient's pregnancy. The patient will also be followed to determine the outcome of the pregnancy. Information on the status of the mother and child will be forwarded to GSK. Generally, follow-up will be no longer than 6 to 8 weeks following the estimated delivery date. Any premature termination of the pregnancy will be reported.

While pregnancy itself is not considered to be an AE or SAE, any pregnancy complication or elective termination of a pregnancy for medical reasons will be recorded as an AE or a SAE, as described in Section 10.6, "Recording of AEs and SAEs" and will be followed as described in Section 10.8, "Follow-up of AEs and SAEs."

A spontaneous abortion is always considered to be a SAE and will be reported as described in Section 10, "Adverse Events (AE) and Serious Adverse Events (SAE)." Furthermore, any SAE occurring as a result of a post-study pregnancy and is considered reasonably related to the investigational product by the investigator, will be reported to GSK as described in Section 10.11, "Post-study AEs and SAEs." While the investigator is not obligated to actively seek this information in former study participants, he/she may learn of an SAE through spontaneous reporting.

#### **6.2.6. Pharmacogenetic sampling**

A whole blood sample (10ml) will be collected (in addition to any blood samples to be taken for the clinical study). Site staff must add the subject number to the specimen tube

(if a pre-printed label does not have the subject number). The blood sample will be taken on a single occasion (unless a duplicate sample is required due to inability to utilise the original sample). It is recommended that the blood sample be taken at the first available opportunity after randomisation (V2) but may be taken at any time during the study after randomisation.

### **6.3. Efficacy**

Sample handling and shipping instructions will be provided separately.

#### **6.3.1. Primary Efficacy**

##### **6.3.1.1. Plaque Lp-PLA2 Activity**

The study medication dosing period is 14(+/- 4) days. The end of the study medication dosing period will coincide with the planned carotid endarterectomy for each patient according to local institution surgical guidelines. A patient will take their last dose of study medication the day before carotid endarterectomy.

Carotid endarterectomy is not a study-specific procedure and will be performed by a suitably qualified surgeon according to local practice.

The investigator, or designate, will be adequately trained on how to handle the excised plaque correctly. The collected plaque will be rinsed in saline solution, to remove blood traces and clots. The plaque will then be immediately frozen in liquid nitrogen and sent to Quest Diagnostics using dry ice transport. Quest Diagnostics will store the frozen samples and ship to GSK laboratories for analysis of Lp-PLA2 activity. Full details of the plaque handling and transport procedure will be provided separately.

#### **6.3.2. Secondary**

##### **6.3.2.1. Plasma Lp-PLA2 activity**

A blood sample will be collected by the investigator, or designate, at Visits 2, and at V4 (or V3 as described in Table 1), V5, V6, V7 for measurement of Lp-PLA2 activity.

- Fasting blood samples for Lp-PLA2 are drawn at V2, V4 (or V3 pre-dose only), V5 and V7
- Non fasting blood samples Lp-PLA2 are drawn at V6 and V4 (V3) post dose only.

Separated plasma will be shipped to a central laboratory (Quest Diagnostics) for storage. Analysis will take place at GSK laboratories.

#### **6.3.2.2. Plasma and plaque Lp-PLA2 mass**

Blood samples collected at Visits 2, 4, (or V3, as described in Table 1) 5, 6, 7, and extracted carotid plaque samples will be sent to Quest Diagnostics and then onto a GSK laboratory for the analysis for Lp-PLA2 mass at a central laboratory (GSK).

#### **6.4. Biomarker(s)**

At Visits 2, 3, 5 and 7, the investigator, or designate, will collect and handle fasting blood samples for: Total cholesterol; high density lipoprotein (HDL); low density lipoprotein (LDL); triglycerides; high sensitivity C-reactive protein (hsCRP); CD40 ligand (CD40L); soluble intracellular adhesion molecules (sICAM); E-selectin; plasminogen activating inhibitor type 1 (PAI-1) activity and antigen; matrix metalloproteinase-9 (MMP-9). In addition, at visit 5, oxidised lipids, their metabolites including lyso-PC will be included in the analysis.

All samples will be analysed by suitably qualified central laboratories. The plaque oxidised lipids and their metabolites including lyso-PC will be analysed by an independent suitably qualified laboratory.

- Plaque samples removed during carotid endarterectomy will be analysed for concentrations/expression of the following biomarkers at a central laboratory (GSK): CD68 (Macrophages); CD3 (T cells); CD20 or 22 (B cells);  $\alpha$ -actin (smooth muscle cells); CD40L; MMP -2 and -9; PAI -1; ICAM; IL-6; Lp-PLA2 (mRNA expression),  $\beta$ -actin, GAPDH (Glyceraldehyde 3-Phosphate dehydrogenase) Axor 18 (a 7 Transmembrane Receptor), and Cyclophilin, oxidised lipids and their metabolites including lyso-PC.

In the event that there is insufficient plaque material to be able to carry the above analysis, lyso-PC will be omitted from the analysis.

Sample handling and shipping instructions will be provided separately.

#### **6.5. Pharmacokinetics and Pharmacodynamics**

##### **6.5.1. PK/PD Sampling Schedule**

All patients will participate in the PK/PD pharmacokinetic sampling. Blood samples for analysis will be collected as described in Table 1.

**Table 1 PK/PD Sampling Schedule**

| Sampling Times                 | Rationale             | Visit 4 
Day prior to
surgery
(after
admission) | Visit 6
Day after
surgery |
|--------------------------------|-----------------------|-------------------------------------------------------------------------|---------------------------------|
| Just before dose               | Trough Conc.          | X                                                                       | —                               |
| 0.5-2 h after dose             | Absorption
Phase   | X                                                                       | —                               |
| 2.5-4 h after dose             | Peak Conc.            | X                                                                       | —                               |
| 6-12 h after dose              | Distribution
Phase | X                                                                       | —                               |
| Any time prior to
discharge | Elimination
Phase  | —                                                                       | X                               |

1. if hospital practice does not allow PK/PD sampling to occur at the specified timepoints during Visit 4, where possible the sampling should be incorporated into the previous visit (3) when study medication is taken in clinic.

Visit 4 can be conducted by telephone, provided PK sampling has been carried out at V3. Patients not attending the Hospital for V4 will be telephoned to confirm that the subject will take their last dose of study medication with food in the morning of visit 4 (the day immediately prior to surgery). The patient should be reminded that Visit 5 is a fasting visit and the patient must not eat or drink with the exception of water, after 11pm on visit 4.

Patients attending the Hospital for visit 4, will be instructed not to take their dose of study medication until after admission to hospital.

The first PK and PD (Lp-PLA2) blood sample at Visit 4 will be collected just before taking study medication. The time of dosing and sample collection will be recorded in the CRF and samples taken within the following time windows:

- 0.5 - 2 hours post dose
- 2.5 - 4 hours post dose
- 6 - 12 hours post dose

If it is not logistically possible to take the PK/PD (Lp-PLA2) samples during Visit 4 (0.5 - 2, 2.5 - 4; and 6 - 12 hours post dose) because the patient is unable to arrive early in the Hospital, then these samples can be taken at Visit 3.

The final PK blood samples will be taken at any time on the day after surgery

Lp-PLA2 Blood sampling: A single blood sample will be collected at V2, V5, V6 and V7. At Visit 4 (or V3 if it is not logistically possible to take these samples at V4) blood samples will be collected as described in Table 1 (Pre-dose, 0.5 –2hr, 2.5 –4hr and 6 - 12hr).

Every effort should be made to collect samples at times spread throughout the time window (i.e., avoid collections from all patients at the same time within a window or only at the extremes of a time window).

In addition to PK/PD samples, another blood sample will be taken at each timepoint. At the end of the study, if appropriate, these samples may be used to measure levels of some of the defined biomarker(s) (Section 6.4) which have demonstrated a change throughout the course of the study.

Samples will be prepared and shipped to Quest Diagnostics. Full details will be provided separately. Quest Diagnostics will store and ship the samples to GSK, where they will be analysed using approved assay techniques.

## **7. INVESTIGATIONAL PRODUCT(S)**

### **7.1. Description of Investigational Product**

SB-480848 will be provided by GSK as a pink, film coated tablet containing 20mg of SB-480848. Matching placebo tablets, indistinguishable in appearance from the SB-480848 tablets, will also be provided by GSK.

### **7.2. Dosage and Administration**

At Visit 2, patients will be randomised to one of three dose groups:

- SB-480848 40mg
- SB-480848 80mg
- Matching placebo

Patients will be provided with 2 bottles and will take 2 tablets from each bottle per day. Patients will continue with their allocated dose group for the 14+/-4 day treatment period.

Study medication should be taken in the morning with food. If PK/PD assessments are to be made during Visit 4 (Day Prior to Surgery) patients should delay taking study medication until instructed to do so after admission to hospital.

On fasting visit days, morning doses of study medication will be taken in the clinic after all fasting laboratory specimens have been obtained.

### **7.3. Dose Rationale**

PK/PD modelling has been undertaken to assess the dose/drug concentration/plasma Lp-PLA2 enzyme activity inhibition relationship for SB-480848. Modelling and simulation suggest that peak and trough inhibition of plasma Lp-PLA2 enzyme activity appear to begin to plateau at doses around 80 mg. It is anticipated that once daily doses of 80 and 40 mg SB-480848 are likely to result in approximately 85-90% and 60-65% trough (24-hour post-dose) plasma Lp-PLA2 enzyme inhibition at steady state, respectively. The

level of correlation between plaque and plasma enzyme inhibition is not known, however, this will be investigated in the study.

### 7.3.1. Pharmacogenetics

Pharmacogenetics (PG) is a study of variability in drug response due to hereditary factors in different populations. There is increasing evidence that an individual's genetic composition (ie. his or her genotype) may impact on drug response or clinical outcome

The aim is to look at the impact of genetic variation on response of SB-480848. This may include trying to identify any genetic markers (variation in a number of genes) that could predict the outcome of investigational treatment response (safety and/or efficacy).

This genetic research is not designed to determine whether other members of the patient's family are at risk of developing atherosclerosis. Neither is the research designed to generate information relevant to the patient's decision regarding whether or not to have children. Participation in the pharmacogenetic portion of the protocol is voluntary and is independent of participation in the core protocol.

### 7.4. Blinding

SB-480848 and matching placebo will be provided for blinding purposes as tablets that will be indistinguishable in appearance. Neither the patient nor the investigator will know which study medication the subject is receiving.

Individual code-breaks will be provided to the investigator. Each code-break will identify the container number and will include an unblinding panel which can be removed by scratching with a coin to reveal the container contents.

**Only in the case of an emergency**, when knowledge of the investigational product is essential for the clinical management or welfare of the patient, the investigator may unblind a patient's treatment assignment. If the blind is broken for any reason, the investigator must notify GSK **immediately** of the unblinding incident without revealing the patient's study treatment assignment. In addition, the investigator will record the date and reason for revealing the blinded treatment assignment for that patient in the appropriate CRF.

If a serious adverse event (SAE; as defined in Section 10.2, "Definition of a SAE") is reported to GSK, Global Clinical Safety and Pharmacovigilance (GCSP) staff may unblind the treatment assignment for the individual patient. If an expedited regulatory report to one or more regulatory agencies is required, the report will identify the patient's treatment assignment. When applicable, a copy of the regulatory report may be sent to investigators in accordance with relevant regulations, GSK policy, or both.

### 7.5. Treatment Assignment

Patients will be assigned to study treatment in accordance with the randomisation schedule. The randomisation schedule will be generated by the GSK statistician.

The Registration and Medication Ordering system (RAMOS) is a telephone based system which will be used to register patients, randomise patients, and allocate double blind medication bottles. Randomisation will be stratified according to statin use and gender.

Please note that the order of drug dispensing will not always be in sequential order.

Note: This telephone call is very important since it will be the only mechanism of identifying which study medication will be assigned to a patient. In addition, this system tracks all shipments of study medication and will also be responsible for resupplies.

The following calls must be made by the investigator (or designee) to RAMOS to perform the following functions:

|              |                                                                                                                                                                                     |
|--------------|-------------------------------------------------------------------------------------------------------------------------------------------------------------------------------------|
| Visit One    | Registration for study SB-480848/010                                                                                                                                                |
| Visit Two    | Randomisation to one of three treatment arms and allocation of appropriate bottle numbers.

At randomisation, patients will be stratified according to statin use and gender. |
| As necessary | Notification of withdrawal from the study                                                                                                                                           |

All calls to RAMOS are confirmed with faxes which are sent to the investigator upon completion of each call. Detailed RAMOS user instructions and worksheets will be provided at study start. All RAMOS faxes and worksheets must be retained in the Investigator's study file.

## **7.6. Packaging and Labeling**

SB-480848 or matching placebo tablets will be supplied in bottles containing tablets of 480848 20mg or placebo to match for 18 days plus 2 days overage.

The container number on the study medication treatment pack will also be recorded in the CRF.

The contents of the label will be in accordance with all applicable regulatory requirements.

Labels for study medication will be printed in the local language. Details included on the labels are as follows:

- Container number
- Quantity statement
- Protocol number
- Dosing instructions

- Storage conditions
- "Keep out of reach of children"
- "For Clinical Trial Use only"
- Company Address
- Expiry Date

### **7.7. Preparation**

No additional preparation required.

### **7.8. Handling and Storage**

Investigational product must be dispensed or administered according to procedures described herein. Only patients enrolled in the study may receive investigational product, in accordance with all applicable regulatory requirements. Only authorized site staff may supply or administer investigational product. All investigational products must be stored in a secure area with access limited to the investigator and authorized site staff and under physical conditions that are consistent with investigational product-specific requirements.

Prior to dispensing, all study medication will be kept safely locked in a dry place at controlled room temperature (20-25°C).

### **7.9. Product Accountability**

The investigator is responsible for investigational product accountability, reconciliation, and record maintenance. In accordance with all applicable regulatory requirements, the investigator or designated site staff must maintain investigational product accountability records throughout the course of the study. This person(s) will document the amount of investigational product received from GSK, the amount supplied and/or administered to and returned by patients, if applicable.

A log for recording receipt of and use of study medications will be maintained by the designated personnel at the Investigator site.

### **7.10. Assessment of Compliance**

The number of tablets dispensed at Visit 2 as well as the calculated percent compliance for study medication will be recorded in the CRF. The percentage compliance may be read from a table provided in the CRF. The following calculation has been used:

$$\frac{\{\text{No. dispensed} - \text{No. returned}\}}{\text{No. of tablets to be taken per day} \times \text{No. days since the last visit}} \times 100$$

The investigator will not be required to complete the above equation but will still be required to record whether compliance was  $\geq 80\%$  and  $\leq 120\%$ .

Patients will be instructed to return any unused study medication at the end of the treatment period.

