### 11.5. Analysis Populations

The populations to be evaluated are:

- modified intent-to-treat: patients receiving at least one-dose of study medication and having valid Lp-PLA2 activity data from carotid plaque.
- intent-to-treat: patients receiving at least one-dose of study medication and having at least one efficacy assessment post-randomisation
- evaluable: subset of modified intent-to-treat population of patients who have at least 10 days of study medication, are between 80 and 120% compliant with medication, as defined in Section 11.6.3, and have carotid endarterectomy surgery within 24 hours of last dose of study medication.
- safety: patients receiving at least one dose of study medication.

For efficacy, the modified intent-to-treat population is of primary interest. The primary analysis will be repeated in the evaluable patient population as a sensitivity check. If the analyses are consistent then all plaque efficacy analyses will be performed on the modified intent-to-treat population only. If the analyses are inconsistent then data from non-evaluable patients will be reviewed in detail to identify the reason for the discrepancy, if possible. Unless a reason for discrepancy is apparent other analyses will be repeated in both populations. For plasma efficacy analyses the dropout rate and possible relation of the dropout pattern to treatment group will be assessed. If appropriate, plasma efficacy analyses may be repeated for the intent-to-treat population.

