### **11.8.1. Extent of Exposure**

A frequency distribution of the number of days of treatment completed by the patients will be produced by treatment group. Total dose received by each subject will be summarised by treatment group. Patients with treatment compliance below 80% or above 120% will be listed.

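### In the 40 mg arm a single tablet count over one active and one placebo bottle does not bound the active dose taken, which weakens the evaluable set and the exposure summary

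*Protocol*

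**What the plan says.** **Product and dosing.** Section 7.1: "SB-480848 will be provided by GSK as a pink, film coated tablet containing 20mg of SB-480848". Matching placebo tablets are also supplied. Section 7.2, for all three arms: "Patients will be provided with 2 bottles and will take 2 tablets from each bottle per day". Section 7.6 describes the supply as "bottles containing tablets of 480848 20mg or placebo to match for 18 days plus 2 days overage" and adds: "The container number on the study medication treatment pack will also be recorded in the CRF".

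**Compliance.** Section 7.10 states: "The number of tablets dispensed at Visit 2 as well as the calculated percent compliance for study medication will be recorded in the CRF". Its formula has one term each for tablets dispensed, tablets returned and tablets due per day, and the investigator records whether the result lies within 80-120%. Section 11.6.3 defines compliance again, as 100 times tablets taken over days of dosing. Neither section mentions the two bottles.

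**Use.** Section 11.5 restricts the evaluable population to patients who, among other conditions, "are between 80 and 120% compliant with medication", and points to Section 11.6.3 for the definition. Section 11.8.1 says: "Total dose received by each subject will be summarised by treatment group". It also calls for a listing of patients outside 80-120%.

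**The concern.** The 40 mg arm is the only one in which the two bottles must differ. A missed or extra tablet there may be active or placebo, and one total cannot show which. In the 80 mg and placebo arms every tablet is alike, so the total does give the dose. The same 80-120% criterion therefore means different things in different arms.

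The evaluable analysis is the sensitivity check on the primary result. Under Section 11.5, its agreement with the modified intent-to-treat analysis decides whether other analyses are repeated in both populations. In the 40 mg arm its compliance filter could keep a patient who took well under 80% of the active tablets, or remove one who took them all. The total-dose summary has the same weakness. If returns are not recorded by bottle while the trial runs, an analysis plan cannot recover the information afterwards.

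**Working it through.** The protocol gives no figure of its own on this point to reproduce.

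**Step 1: bottle contents.** Active tablets are 20 mg (Section 7.1). Each patient takes 2 bottles x 2 tablets = 4 tablets a day (Section 7.2). Bottles hold active or placebo tablets (Section 7.6).
- 80 mg: 4 x 20 mg, so both bottles are active.
- Placebo: both bottles are placebo.
- 40 mg: 2 x 20 mg plus 2 placebo, so one bottle of each kind. The protocol does not say this in words, but it follows.

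**Step 2: what a pooled count allows, with neither bottle over-used.** Let D be days of dosing, a the active and p the placebo tablets taken, each at most 2D. Pooled compliance, with the Section 7.10 denominator, is 100 x (a + p)/(4D). The share of the assigned active dose is a/(2D).

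For D = 14, 56 tablets are due, 28 of them active. Since 44/56 = 78.6% and 45/56 = 80.4%, at least 45 tablets are needed.
- 28 placebo + 17 active: 80.4% pooled; 17/28 = 60.7% of the active dose (340 of 560 mg, about 24 mg/day).
- 17 placebo + 28 active: 80.4% pooled; 28/28 = 100% of the active dose (40 mg/day).

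The lowest active share that passes the 80% limit, by treatment length:

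| Days | Tablets due | Fewest that pass | Fewest active (all placebo taken) | Share of active dose |
|---|---|---|---|---|
| 10 | 40 | 32 | 12 of 20 | 60.0% |
| 14 | 56 | 45 | 17 of 28 | 60.7% |
| 18 | 72 | 58 | 22 of 36 | 61.1% |

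The converse also occurs. At 14 days, 28 active + 16 placebo is 44/56 = 78.6%, so a patient who took every active tablet is excluded.

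**Step 3: if a bottle can be over-used.** This assumes 40 tablets per bottle (20 days x 2); the protocol states the days of supply but not the tablet count. At exactly 100% pooled compliance, active tablets run from 4D - 40 to 40:
- 10 days: 0 to 40 of 20 (0-200%)
- 14 days: 16 to 40 of 28 (57-143%)
- 18 days: 32 to 40 of 36 (89-111%)

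These are outer limits, reached only by drawing repeatedly from the wrong bottle.

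**Step 4: which formula governs.** The evaluable set uses Section 11.6.3, which omits tablets per day. Read literally, full compliance is 100 x 4D/D = 400%. That is a separate error. The figures above assume it is corrected to the four-tablet denominator, and correcting it alone does not add a bottle term.

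**Step 5: after the fix.** At 14 days, 80-120% on each container means 23 to 33 of 28 tablets, or 82.1% to 117.9% of the assigned active dose.

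**The case against.** Pooling is not stated. The Section 7.10 formula could be applied bottle by bottle, and the CRF table it mentions is not shown. Bottles are individually allocated (Section 7.5), container numbers go into the CRF (Section 7.6), sites document amounts returned (Section 7.9), and code-breaks link container to contents (Section 7.4). This stands in part. A reader might infer that total dose received cannot be computed in the 40 mg arm, and the protocol does not show that. It is fair to say only that the data Section 7.10 specifies do not identify it: a container number without a return count for that container is not enough, and Section 7.9 does not say that returns are logged by container.

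A reader might also infer that the 40 mg versus placebo comparison and the dose-response analysis are compromised. They are not changed by how tablets are counted. The primary analysis uses the modified intent-to-treat set, which has no compliance criterion, and the Section 11.7.3 model uses assigned dose (0, 40, 80). Actual under-dosing could dilute both, but that would be so under any counting rule.

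Unequal use may also be rare. Forgetting a whole day's dose affects both bottles equally, and the pooled figure is then right. Compliance is checked at Visits 3 and 4 (Appendix 1), and all patients give PK samples, which are direct evidence of recent active exposure. These points make the extremes in Step 3 unlikely. They do not replace a count by bottle, because PK samples at one visit do not give tablets taken over the whole course.

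**Conclusion.** The concern holds in a limited form. Under the natural reading of Sections 7.10 and 11.6.3, pooled compliance in the 40 mg arm does not bound the active dose when the bottles are used unequally. At the 80% limit about 60% to 100% of the active tablets may have been taken without over-use of either bottle (60.7% to 100% at 14 days). This rests on the inferred one-active, one-placebo supply, on pooling as the natural but unstated reading, and on a denominator of four tablets a day. The protocol gives no frequency of unequal use, so the number of patients affected cannot be estimated. Only the evaluable sensitivity population, the total-dose summary and the compliance listing are touched. It is a cheap improvement to data collection and not a threat to the primary result.

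**What to change.** 1. In Section 7.10 and the CRF, record tablets dispensed and returned for each container number.
2. In Section 11.6.3, the definition that Section 11.5 relies on, define compliance per container with the tablets due per day from that container in the denominator, and align Section 7.10 with it.
3. For the evaluable set, apply the existing 80-120% window to each container. This needs no knowledge of contents, so the blind is kept.
4. In Section 11.8.1, derive total dose received from the active container or containers after unblinding.

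The cost is one extra CRF line per patient. Some 80 mg or placebo patients whose total was right but unevenly drawn from two identical bottles would leave the sensitivity set. The modified intent-to-treat set is unaffected. A letter on each bottle to tell the two apart is optional.
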